### Recruitment {15}

Potential participants will be recruited from the Denver Metro area. We will recruit using CU-AMC campus wide e-mails, flyers, and research website (which maintains an updated list of available studies performed on campus which is also accessible to the general population). We will also provide flyers to the University of Colorado Primary Care practices as well as other local primary care practices including Denver Health Medical Center which serves low-income and minority populations. The trial is registered at ClinicalTrials.gov. We will also employ social media advertising strategies including the use of BUMP Digital Marketing. BUMP uses social media networks (Facebook, Instagram, etc.) to target a population of interest using an appealing advertisement for the study. The advertisement will include a link to a study landing page providing more information about the study, including a brief description of the study requirements and eligibility criteria. Interested individuals will be provided a link to a screening questionnaire.

### Assignment of interventions: allocation

#### Sequence generation {16a}

The randomization assignment will be generated by the study biostatistician (ZP) using a computer-generated block randomization performed within strata defined by sex. Stratification by BMI, age, and race/ethnicity is not needed; given the large sample size, randomization alone should produce balance in these factors.

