### Sample size {14}

An a priori power calculation was performed for the primary outcome (weight) using nQuery 7.0 (Statistical Solutions Ltd, Cork, Ireland). In our power analyses, we made the following assumptions: (1) power ≥ 0.90 and above for the primary outcome is ideal; (2) the significance level under the null hypothesis will be set at *α* = 0.05; (3) null hypotheses will be tested against two-directional (that is, two-tailed) alternative hypotheses; (4) a 3-kg between-group difference in weight loss was deemed the minimum difference of clinical importance; and (5) the primary analysis will use the intent-to-treat principle in which all randomized participants are analyzed. We will enroll 150 participants (75 participants per randomized group) to provide 90% power at 5% significance to detect a between-group difference of 3 kg in body weight at 52 weeks. With an attrition rate of as high as 20%, we retain 82% power in a sensitivity (completer’s) analysis. Standard deviation (SD) of weight loss used in this calculation was 5.6 kg and was based on a 52-week interventional study using the Colorado Weigh program conducted at our research center [96]. There are no previous data for us to estimate the effect size for any of the outcomes at 52 weeks. If superiority of IMF to DCR cannot be established, we will perform a non-inferiority test using 2.26-kg weight loss as a non-inferiority margin. In this case, we would have 79% power to establish non-inferiority of IMF as compared to DCR assuming no difference in effect of weight loss between the two groups.

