#### Concealment mechanism {16b}

Allocation of treatment will take place after all eligible participants for each cohort have completed baseline measures, based on the a priori randomization list.

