### Statistical methods

#### Statistical methods for primary and secondary outcomes {20a}

Baseline characteristics will be summarized by treatment groups using descriptive statistics. Normality assumptions will be evaluated, and transformations used (e.g., square root and log) as appropriate. Body weight is the primary outcome variable and others are secondary or exploratory outcomes. Consequently, no adjustment for multiple outcomes will be applied. *P*-values < 0.05 will be considered significant. Any imbalance in baseline characteristics between groups that could potentially be a confounding factor for the outcome will be adjusted for in the statistical model.

The primary analysis will use the “intent-to-treat” principle and all randomized participants will be analyzed. Each continuous outcome will be analyzed using a linear mixed effects model. The fixed effects of the linear mixed effects model will consist of treatment group (IMF or DCR) and time of measurement (i.e., baseline and follow-up time points) and their interaction. Time of measurement will be treated as a continuous or categorical variable, as appropriate. Test of the interaction assesses the difference in post-intervention change from baseline between two groups and is used to quantify the effectiveness of the intervention. The 90% confidence interval for the interaction will be calculated. Incidence of adverse events, protocol modifications, and attrition will be compared between groups using chi square or Fisher’s exact test as appropriate.

To explore the impact of selected biologic, psychosocial, behavioral, and/or environmental variables on the intervention effect, we will initially apply models similar to those being tested in aim 1, with the addition of a potential effect moderator as a covariate and its interaction term (i.e., intervention × moderator × time interaction) in addition to related two-way interaction terms. Among factors with a significant three-level interaction, we will further use post-intervention weight loss as the outcome and multiple linear regression to examine their association with the outcome and its interaction with intervention. Similar multiple logistic regression analysis will also be conducted with the outcome dichotomized as responder and non-responder using clinical criteria.

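### Randomisation is stratified by sex, but the primary model omits sex and leaves each arm's baseline mean free: the analysis is valid and slightly conservative, and gives up a modest gain in precision

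*Protocol article*

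**What the plan says.** Sequence generation {16a} specifies "computer-generated block randomization performed within strata defined by sex" and names no other stratum. Concealment mechanism {16b} adds: "Allocation of treatment will take place after all eligible participants for each cohort have completed baseline measures". It ties allocation to a list drawn up in advance.

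Statistical methods for primary and secondary outcomes {20a} fixes the model: "The fixed effects of the linear mixed effects model will consist of treatment group (IMF or DCR) and time of measurement", plus their interaction. Time includes the baseline visit, and the interaction is the treatment effect. The same section says that baseline imbalances which might confound the outcome will be adjusted for. It lists no covariates in advance.

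Sample size {14} powers the trial on weight change: "Standard deviation (SD) of weight loss used in this calculation was 5.6 kg", with 75 per arm, "to provide 90% power at 5% significance to detect a between-group difference of 3 kg in body weight at 52 weeks". It gives 79% power for non-inferiority at a margin of 2.26 kg.

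**The concern.** Two pieces of information that the design supplies are not used.

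- **Sex.** Blocking within sex balances the arms on sex. If sex predicts weight change, this lowers the true variance of the treatment contrast. A model without sex leaves that variation in the residual, so its standard error is a little too large.
- **Baseline weight.** With baseline as an outcome time and a group main effect, each arm's baseline mean is estimated separately. With complete data and categorical time, the week-52 interaction is then the raw difference in change scores. Randomisation makes the two baseline means equal in expectation, and a model that uses this is more precise.

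The imbalance clause does not fill the gap. Stratification makes an imbalance in sex unlikely, so the clause will normally not bring sex in. For other variables it makes the primary model depend on the data observed. At stake is the width of the primary interval, chiefly for the non-inferiority question, where planned power is lowest.

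**Working it through.** **Inputs from Sample size {14}:** difference 3 kg, SD 5.6 kg, 75 per arm, two-sided 5%, non-inferiority margin 2.26 kg. One-sided 5% is used for non-inferiority because it reproduces the stated 79% and matches the 90% interval in {20a}.

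**Inputs that are assumptions** (the document does not give them): the share of change variance explained (R²), the baseline SD, the effect of sex on weight change, and the proportion of women.

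**Step 1: reproduce the plan's figures.** SE = 5.6 × √(2/75) = 0.914 kg.
- Superiority: 3/0.914 = 3.281; Φ(3.281 − 1.960) = 90.7% (noncentral t: 90.3%). Stated: 90%.
- Non-inferiority: 2.26/0.914 = 2.471; Φ(2.471 − 1.645) = 79.6% (noncentral t: 79.3%). Stated: 79%.

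Both follow from the unadjusted SD of change, so the plan counts on no gain from adjustment.

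**Step 2: sex and baseline weight together.** The SE becomes SE × √(1 − R²).

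| Assumed R² | Superiority, normal (t) | Non-inferiority, normal (t) |
|---|---|---|
| 0% | 90.7% (90.3%) | 79.6% (79.3%) |
| 5% | 92.0% (91.7%) | 81.3% (81.0%) |
| 10% | 93.3% (93.0%) | 83.1% (82.9%) |

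At R² = 10%, 150 × 0.90 = 135 participants would give the precision that 150 give unadjusted.

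**Step 3: common baseline mean alone.** Assume equal SDs (SDb) at baseline and week 52. The correlation implied by the SD of change is ρ = 1 − 5.6²/(2 × SDb²), and the variance ratio against the change score is (1 + ρ)/2.
- SDb = 12 kg: ρ = 1 − 31.36/288 = 0.891; ratio 0.946. Superiority 91.8%, non-inferiority 81.2% (noncentral t).
- SDb = 20 kg: ρ = 1 − 31.36/800 = 0.961; ratio 0.980. Superiority 90.9%, non-inferiority 79.9%.

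Against 90.3% and 79.3%, the gain is roughly half a point to two points.

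**Step 4: sex alone.** Assume 75% women and a sex difference in weight change of d kg. Sex then explains d² × 0.75 × 0.25 / 31.36 of the change variance.
- d = 1 kg: 0.6%; reported SE too large by 0.3%; type I error 4.9%.
- d = 2 kg: 2.4%; SE too large by 1.2%; type I error 4.7%.
- d = 2.5 kg: 3.7%; SE too large by 1.9%; type I error 4.6%.

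Here the excess in SE is 1/√(1 − share) − 1, and the type I error is 2 × [1 − Φ(1.96/√(1 − share))].

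Balanced allocation delivers part of the gain even without adjustment. For d = 2 kg the unadjusted test has superiority power Φ((3.281 − 1.960)/√(1 − 0.024)) = 90.9%. With sex in the model it is Φ(3.281/√(1 − 0.024) − 1.960) = 91.3%.

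**The case against.** Several objections carry weight.

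- **The model is acceptable as it stands.** A mixed model with baseline as an outcome and a group-by-time contrast is unbiased in a randomised trial and agrees with the SD used for the sample size. This stands: there is no bias and no inflated error.
- **Covariate lists are often left to an analysis plan.** Here, however, {20a} states what the fixed effects are and adds a rule for choosing covariates, so the article does fix the point.
- **The document provides for adjustment.** A reader might infer that chance baseline differences simply go unaddressed. The imbalance clause in {20a} rules that out, and {20c} allows covariates in one sensitivity analysis. Neither puts sex or baseline weight into the primary model in advance, and the separate reporting of men and women in {20b} does not either.
- **Cohort.** Because allocation is run cohort by cohort, a reader might infer that cohort is a second stratum wrongly left out. The documents do not support this. Only sex is named, allocation follows a list made in advance, and nothing says that blocks close within a cohort. The number of cohorts is not given, so the cost of cohort-by-time terms cannot be called small.
- **The gain is small and assumed.** This stands. No R², baseline SD or sex effect is in the document, and part of the gain from sex is already delivered by the balanced allocation (Step 4).

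**Conclusion.** The point holds as an efficiency and pre-specification issue. The stratifier is missing from the primary model, baseline weight is not used as fully as randomisation allows, and the only route for covariates depends on the data.

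The loss is about 1 to 4 power points under the assumed R² of 5% to 10%. It matters most for the 79% non-inferiority power and little for superiority, where the stated 90% is met without adjustment. These figures set an adjusted model against the plan's own power figures, and they rest on the assumed R².

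A reader might go further and infer that the planned analysis is invalid or the trial underpowered for superiority. The documents support neither: the direction of error is conservative and the stated power reproduces.

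**What to change.** Before the arms are unblinded for analysis, pre-specify the following:

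1. **Baseline.** Use a constrained longitudinal model with one baseline mean for both arms and group-by-time terms at follow-up visits only. An alternative is a mixed model of follow-up weight with baseline weight and baseline-by-time as covariates.
2. **Sex.** Add sex and sex-by-time as fixed effects. With complete data, a main effect of sex alone leaves the change contrast unchanged, so the time interaction is needed.
3. **Covariate rule.** Replace the imbalance-triggered adjustment with this fixed set.
4. **Cohort.** Optional, for example as a sensitivity analysis.

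**Cost:** a change of wording and a few degrees of freedom. With five visits and categorical time, sex and sex-by-time take 1 + 4 = 5 parameters, and a common baseline mean saves one. Both variables are already available for every randomised participant: sex from the stratification and weight from the baseline visit.

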#### Concealment mechanism {16b}

Allocation of treatment will take place after all eligible participants for each cohort have completed baseline measures, based on the a priori randomization list.

#### Implementation {16c}

The study biostatistician will generate the allocation sequence. After all participants have completed screening and baseline assessments, participants will be notified of the randomization assignment on the first day of group class for the intervention. This process will take place separately within each cohort.

### Assignment of interventions: blinding

#### Who will be blinded {17a}

Due to the nature of the intervention, it is not plausible to blind participants. However, participants will be blinded to the study hypothesis. Due to the nature of the group-based behavioral intervention, it is also not plausible to blind study staff who enroll participants and deliver or monitor intervention delivery. However, the following personnel will be blinded to study group assignment: (1) staff performing laboratory analyses, (2) DLW assessment core staff performing analysis of the DLW samples, and (3) Colorado Clinical and Translational Sciences Institute Nutrition Core personnel who will be using Nutrition Data System for Research software to analyze the 7-day diet diary data. Lastly, all data analyses and reporting will be completed by study investigators who are blinded to study arm assignments.

#### Procedure for unblinding if needed {17b}

Study personnel who are responsible for analyzing data and reporting results will remain blinded throughout the study period.

### Data collection and management

#### Plans for assessment and collection of outcomes {18a}

Outcome measures will be assessed during in-person clinic visits with trained, research staff. We will use detailed data collection forms to promote data quality and reduce assessor error. Weight, blood pressure, and waist circumference will be measured twice and the average of the two measures will be used in analyses. Questionnaires will be administered online using REDCap survey or Qualtrics. Scores from questionnaire responses will be calculated directly within REDCap using hidden, calculated fields. See Table 4 for a list of each study questionnaire and the questionnaire references.

#### Plans to promote participant retention and complete follow-up {18b}

The study coordinators will be responsible for establishing and maintaining contact with participants throughout the study. At enrollment, contact information will be obtained including alternate phone numbers and a phone number of a relative/friend who will always know the participant’s whereabouts. If study appointments are missed, the study coordinator will follow-up with a telephone call to reschedule. If participants miss two group-based support classes in a row without prior communication, study coordinators will contact participants to discuss attendance. In our experience, the most important characteristics of high retention is frequent and high-quality interaction with key study staff. We will ensure continuity of key staff during the entire study so that participants build a relationship with study personnel, to provide inspiration and increase accountability. Participants will also be compensated for completing study outcome measures.

#### Data management {19}

Field and range checks will be programmed to minimize data entry errors. Data distribution will be checked periodically, and outliers verified; missing data will be tracked and checked. All data will be entered into the REDCap database and will be sight verified by a second study staff member.

#### Confidentiality {27}

A participant identifier code for the data will be used so that data will not have the participant’s name associated with it. The key linking participant name and participant identifier code is kept in a secured location, with only key personnel having direct access to the list. Participant identifier codes will be used for all data entry and data analyses. The investigative team will be trained in accordance to both the Colorado Multiple Institutional Review Board (COMIRB) and the Health Insurance Portability and Accountability Act (HIPAA) compliance issues and will act to maintain confidentiality and protect health information. Electronic data will be stored on secure servers with a high level of security, controlled access, daily back-up, and long-term retention of back-up files. Hard copies of study data will be kept in in participants’ charts in a locked, secured file cabinet in the principal investigator’s or study coordinator’s office. Access to all study data will be restricted to the principal investigator and research personnel.

#### Plans for collection, laboratory evaluation, and storage of biological specimens for genetic or molecular analysis in this trial/future use {33}

Blood samples will be collected at baseline and weeks 13, 26, 52, and 78 and will be stored securely until funds are available to support future ancillary studies, including genetic/epigenetic or molecular analyses. Stool samples will be self-collected by study participants at baseline and weeks 13, 26, 52, and 78 using the Alpco EasySampler Stool Collection Kit. Participants will sterilely transfer ~1–2 g of stool to the provided collection tubes, store specimens at −20 °C (home freezers), and transport them to the clinic on icepacks within a week of collection. Blood and stool specimens will then be stored at −80°C for future analyses.

### Statistical methods

#### Statistical methods for primary and secondary outcomes {20a}

Baseline characteristics will be summarized by treatment groups using descriptive statistics. Normality assumptions will be evaluated, and transformations used (e.g., square root and log) as appropriate. Body weight is the primary outcome variable and others are secondary or exploratory outcomes. Consequently, no adjustment for multiple outcomes will be applied. *P*-values < 0.05 will be considered significant. Any imbalance in baseline characteristics between groups that could potentially be a confounding factor for the outcome will be adjusted for in the statistical model.

The primary analysis will use the “intent-to-treat” principle and all randomized participants will be analyzed. Each continuous outcome will be analyzed using a linear mixed effects model. The fixed effects of the linear mixed effects model will consist of treatment group (IMF or DCR) and time of measurement (i.e., baseline and follow-up time points) and their interaction. Time of measurement will be treated as a continuous or categorical variable, as appropriate. Test of the interaction assesses the difference in post-intervention change from baseline between two groups and is used to quantify the effectiveness of the intervention. The 90% confidence interval for the interaction will be calculated. Incidence of adverse events, protocol modifications, and attrition will be compared between groups using chi square or Fisher’s exact test as appropriate.

To explore the impact of selected biologic, psychosocial, behavioral, and/or environmental variables on the intervention effect, we will initially apply models similar to those being tested in aim 1, with the addition of a potential effect moderator as a covariate and its interaction term (i.e., intervention × moderator × time interaction) in addition to related two-way interaction terms. Among factors with a significant three-level interaction, we will further use post-intervention weight loss as the outcome and multiple linear regression to examine their association with the outcome and its interaction with intervention. Similar multiple logistic regression analysis will also be conducted with the outcome dichotomized as responder and non-responder using clinical criteria.

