**Methods:**

The *D*aily Caloric *R*estriction vs. *I*ntermittent *F*asting *T*rial (DRIFT) is a two-arm, 52-week block randomized (1:1) clinical weight loss trial. The two intervention arms (DCR and IMF) are designed to prescribe an equivalent average weekly energy deficit from baseline weight maintenance energy requirements. Both DCR and IMF will be provided guideline-based behavioral support and a PA prescription. The primary outcome is change in body weight at 52 weeks. Secondary outcomes include changes in body composition (dual-energy x-ray absorptiometry (DXA)), metabolic parameters, total daily energy expenditure (TDEE, doubly labeled water (DLW)), EI (DLW intake-balance method, 7-day diet diaries), and patterns of physical activity (PA, activPAL device).

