### Objectives {7}

The aims of DRIFT are to (1) compare changes in body weight (primary outcome), body composition, and metabolic parameters induced by IMF and DCR; (2) evaluate the impact of IMF vs. DCR on EI and dietary adherence; and (3) evaluate the impact of IMF vs. DCR on energy expenditure (EE) and patterns of PA. Informed by our prior IMF pilot study that suggested that IMF may be better for long-term weight loss maintenance vs. DCR [15], our a priori hypotheses are that IMF will generate greater weight loss (primary outcome), greater decreases in fat mass, improved maintenance of lean mass, and greater improvements in metabolic parameters (fasting lipids, insulin sensitivity, blood pressure) at 52 weeks. While these hypotheses are contrary to recently published data from long-term studies, these data were not available at the time the study was designed. We also will use the National Institutes of Health (NIH) Accumulating Data to Optimally Predict obesity Treatment (ADOPT) framework to evaluate selected biologic, behavioral, environmental, and psychosocial predictors of weight loss response [24–28].

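### Having one primary outcome is used to call any p < 0.05 significant, including on the five secondary items under a priori hypotheses; the word should be kept for week-52 weight

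*Protocol article*

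**What the plan says.** The section on statistical methods for primary and secondary outcomes {20a} first sets the ranking: "Body weight is the primary outcome variable and others are secondary or exploratory outcomes". It draws a conclusion from that ranking: "Consequently, no adjustment for multiple outcomes will be applied". It then says of P-values that "values < 0.05 will be considered significant". That sentence names no outcome.

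The Objectives section {7} lists more than weight among its prior expectations. The sentence starts with "our a priori hypotheses are that IMF will generate greater weight loss (primary outcome" and continues, for the same 52-week time point, with "greater decreases in fat mass, improved maintenance of lean mass, and greater improvements in metabolic parameters (fasting lipids, insulin sensitivity, blood pressure". The primary-outcome tag is attached to weight alone.

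The Methods part of the abstract gives a longer secondary list: "Secondary outcomes include changes in body composition (dual-energy x-ray absorptiometry (DXA)), metabolic parameters, total daily energy expenditure", followed by energy intake and physical activity. The Sample size section {14} makes testing two-sided and powers weight only.

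The article gives no testing order, no allocation of alpha, and no statement that secondary p-values are descriptive.

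**The concern.** The inference from one primary outcome to no adjustment is sound for weight: with a single primary comparison there is nothing to adjust. It says nothing about the error rate across the other outcomes, yet the significance rule that follows covers them too. A plan may leave secondary outcomes unadjusted if their p-values are read as nominal, but this text attaches the word significant to them instead.

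This matters here because several secondary outcomes carry a stated directional hypothesis. The Objectives section also concedes that its hypotheses run against recently published long-term data, so a trial without superiority on weight is a realistic outcome. A secondary result that crosses 0.05 by chance could then be reported, in keeping with the plan, as a significant advantage of one diet.

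**Working it through.** **Inputs from the protocol.** Two-sided tests at 0.05 (Sample size; Statistical methods). Weight: 75 per arm, difference 3 kg, SD 5.6 kg, attrition up to 20%, which leaves 60 per arm (Sample size). Five hypothesised secondary items (Objectives).

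**Assumptions.** The protocol gives neither the number of secondary tests nor their correlations. I use five tests, as named, and nine tests if lipids are split into four fractions and systolic and diastolic pressure are tested separately (fat mass 1 + lean mass 1 + lipids 4 + insulin sensitivity 1 + blood pressure 2 = 9). Correlations are taken as equal, from 0 to 0.9, and every null hypothesis as true.

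**Step 1: the plan's own figures.** The protocol states no familywise error rate; its related figures are powers. For a two-sample t-test the noncentrality is (3/5.6) × √(n/2). With n = 75 it is 3.28 and power is 90.3% (stated 90%). With n = 60 it is 2.93 and power is 82.9% (stated 82%). The stated figures are reproduced to within a point.

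**Step 2: independent tests.** The chance of at least one p < 0.05 among k tests is 1 − 0.95^k.
- k = 5: 1 − 0.95^5 = 22.6%
- k = 9: 1 − 0.95^9 = 37.0%

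**Step 3: correlated tests.** For k standard normal statistics with common correlation ρ, and c = 1.96, the chance is

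1 − ∫ [Φ((c − √ρ·x)/√(1−ρ)) − Φ((−c − √ρ·x)/√(1−ρ))]^k φ(x) dx.

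| ρ | five tests | nine tests |
|---|---|---|
| 0 | 22.6% | 37.0% |
| 0.3 | 20.9% | 32.6% |
| 0.5 | 18.3% | 26.9% |
| 0.7 | 14.8% | 20.2% |
| 0.8 | 12.7% | 16.6% |
| 0.9 | 10.2% | 12.3% |

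Simulation of the nine-test case at ρ = 0.5, 0.6 and 0.7 gave 26.9%, 23.6% and 20.3%, in agreement with the integral (26.9%, 23.7%, 20.2%).

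**Step 4: false claims in one direction only.** Counting only chance results that favour intermittent fasting (0.025 per test, independent): 1 − 0.975^5 = 11.9% and 1 − 0.975^9 = 20.4%.

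**Step 5: what formal control would cost.** The strictest Holm step for nine tests is 0.05/9 = 0.0056. Take a secondary effect of 0.5 SD (an assumption, close to the planned 3/5.6 = 0.54 SD for weight) and the same t-test power:
- 75 per arm: 86% at 0.05, 60% at 0.0056
- 60 per arm: 78% at 0.05, 47% at 0.0056

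**The case against.** The strongest reply is that this is a common and openly stated convention. One outcome is named primary, only that outcome is powered, all others are labelled secondary or exploratory, and the absence of adjustment is declared. Nothing is miscalculated, and insisting on a multiplicity procedure for secondary outcomes would be a preference. That stands, and it is why the point concerns wording only. It does not rescue the 0.05 sentence, because the convention relies on secondary p-values being read as nominal and this text calls them significant.

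The article is condensed, and a separate analysis plan may rank secondary outcomes or describe their p-values as nominal. That is possible. Such a plan would still have to be reconciled with the published sentence, which states a rule and does not leave the matter open.

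It is also fair that no text says secondary results will be presented as confirmed benefits. The harm depends on how results are reported, and the plan permits it without requiring it.

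A reader might go further and infer that the protocol lists nine hypothesised outcomes with a 20 to 37% chance of a false claim. It does not. It names five items, and the lipid panel is not broken into fractions where it is specified. The value of 20% is not a floor either: it belongs to nine tests at correlation 0.7, and the same nine give 12.3% at 0.9.

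**Conclusion.** The point holds in a limited form. The reason given for not adjusting covers the weight comparison alone, while the significance rule covers every outcome, including five under a priori hypotheses. With all nulls true, the chance of at least one p < 0.05 is about 10 to 23% for the five named items and about 12 to 37% for the assumed nine. Across everything examined with two-sided tests, this is at least about twice 5%. The figures rest on equal correlations between 0 and 0.9 and on the stated counts, neither of which the protocol supplies.

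A reader might infer that the trial's main conclusion is compromised. The documents do not support that: the error rate for week-52 weight is unaffected. Nor do they support the view that leaving secondary outcomes unadjusted is in itself an error. What needs correcting is the use of the word significant for them.

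**What to change.** In the statistical methods section {20a}, apply the rule that P-values below 0.05 are significant to the primary week-52 weight comparison only. State that all secondary and exploratory outcomes will be reported as estimates with confidence intervals and nominal p-values, without claims of significance. The same section already plans a confidence interval for the group-by-time interaction, so no new analysis or data are needed. The cost is fewer formal secondary claims: a secondary p below 0.05 becomes a nominal finding.

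If formal claims on the hypotheses in the Objectives are wanted, those week-52 outcomes can be listed as one closed family and tested by Holm. This is optional. At its strictest step for nine tests it lowers power for a 0.5-SD effect from about 86% to 60% with 75 per arm, or from 78% to 47% with 60 per arm. It is credible only if the family is fixed and dated before unblinded analysis. Timing matters: the Trial status section expects week-78 measures to end by 12/19/2022, and 26 weeks earlier is about June 2022, so week-52 visits were probably near complete when the article appeared in August 2022. The plan to keep analysts blinded to arm leaves room for such a clarification, provided that blinding still held.
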